## Abstract

**Background:** Hearing impairments are associated with reduced walking performance under Dual-task (DT) conditions. Little is known about the neural representation of DT performance while walking in this target group compared to healthy controls or younger adults. Therefore, utilizing the Mobile Brain/Body Imaging approach (MoBI), we aim at gaining deeper insights into the brain dynamics underlying the interaction of cognitive and motor processes during different DT conditions (visual and auditory) controlling for age and the potential performance decrements of older adults with hearing impairments.

**Methods:** The cross-sectional study integrates a multifactorial mixed-measure design. Between-subject factors grouping the sample will be age (younger vs. older adults) and hearing impairment (mild vs. not hearing impaired). The within-subject factors will be the task complexity (single- vs. DT) and cognitive task modality (visual vs. auditory). Stimuli of the cognitive task will vary according to the stimulus modality (visual vs. auditory), presentation side (left vs. right), and presentation-response compatibility (ipsilateral vs. contralateral). Analyses of DT costs and underlying neuronal correlates focus either on gait or cognitive performance. Based on an *a priori* sample size calculation 96 (48 healthy and 48 mildly hearing impaired) community-dwelling older adults (50–70 years) and 48 younger adults (20–30 years) will be recruited. Gait parameters of speed and rhythm will be captured. EEG activity will be recorded using 64 active electrodes.

**Discussion:** The study evaluates cognitive-motor interference (CMI) in groups of young and older adults as well as older adults with hearing impairment. The underlying processes of the interaction between motor and cognitive tasks will be identified at a behavioral and neurophysiological level comparing an auditory or a visual secondary task. We assume that performance differences are linked to different cognitive-motor processes, i.e., stimulus input, resource allocation, and movement execution. Moreover, for the different DT conditions (auditory vs. visual) we assume performance decrements within the auditory condition, especially for older, hearing-impaired adults. Findings will provide evidence of general mechanisms of CMI (ST vs. DT walking) as well as task-specific effects in dual-task performance while over ground walking.

## Introduction

Age-related decline in hearing is one of the most common chronic conditions in older adults, affecting nearly half of people over the age of 65 (Goman and Lin, 2016). In recent decades, a worldwide increase in the prevalence of hearing impairments has been observed. With 42 million people affected worldwide in 1985 (∼0.8%), the number increased more than eightfold to 360 million in 2011 (∼5.2%, Olusanya et al., 2014; Olusanya et al., 2019). According to current research, this number grew further to 466 million people (∼6.1%) in 2018 and is estimated to increase to 900 million in 2050 (World Health Organization, 2020). These numbers emphasize the increasing importance of hearing impairment as a public health burden.

Longitudinal studies have shown that hearing impairment is independently associated with poorer cognitive performance even when controlling for age and sex (Valentijn et al., 2005; Lin, 2011). Several researchers have tried to explain this association between age-related hearing impairment and cognitive decline (cf. Mudar and Husain, 2016). Some have proposed a common cause hypothesis, which explains hearing impairment and cognitive decline as a widespread neural degeneration that occurs during aging. Others have proposed an information degradation hypothesis, which suggests poorer cognitive performance as a result of hearing impairment. Presumably, additional cognitive resources are devoted to auditory processing, resulting in fewer resources available for other processes. The sensory deprivation hypothesis views poorer cognitive performance not as an instantaneous consequence of the hearing impairment as the information degradation hypothesis does, but as a long-term change in brain plasticity (Mudar and Husain, 2016).

Age-related changes in the auditory system can include both, higher pure-tone detection thresholds and supra-threshold auditory difficulties (Schneider et al., 2010), requiring a more deliberate allocation of resources to hearing. Consequently, hearing becomes more effortful and cognitively demanding (Pichora-Fuller et al., 2016). Beyond hearing difficulties, hearing impairment further affects physical activities (Chen et al., 2014; Gispen et al., 2014). As a result of cognitive and physical challenges, hearing impairment negatively affects several aspects of one’s personal and social life, such as psychosocial well-being, quality of life, economic independence, and interpersonal communication (Mick et al., 2014). Frequently observed consequences encompass social isolation and stigmatization, substance abuse, psychiatric disturbance, depression, difficulties in relationships with partners and children as well as occupational stress (Olusanya et al., 2019). Moreover, activities of daily living (ADL) are further aggravated by hearing impairments in older adults (Chang et al., 2009; Gopinath et al., 2016). Effects of age-related hearing impairment on locomotion and cognition were examined in comparison to age-matched reference groups with hearing-impaired older adults exhibiting lower levels of physical activity and functional performance (Chen et al., 2014; Gispen et al., 2014). A decline in hearing has been found to correlate with balance impairments (Viljanen et al., 2009a,b), self-reported walking limitations (Chen et al., 2014), poor endurance (Gopinath et al., 2016), and increased frailty (Kamil et al., 2014). There are also findings on gait parameters that accompany hearing impairment. An increasing deficit of auditory perception has been found to negatively affect stride length as well as gait speed and cadence under dual-task conditions, independent of age and comorbidities (Wollesen et al., 2018). The effects of hearing impairment on gait even exceed the influence of age, disease, and previous falls (Lin and Ferrucci, 2012). Furthermore, both hearing impairment and decrements in gait quality are associated with the risk of falling in older adults (Lin and Ferrucci, 2012; Jiam et al., 2016).

Researchers have attempted to explain the association between hearing impairment and mobility decline in terms of competition for limited shared cognitive resources (Bruce et al., 2019). In everyday life, balancing or walking is rarely the only task performed at a time (single-task) and it is mostly performed together with another task (dual-task) or sometimes even as a multitasking activity (Faulkner et al., 2007). Cognitive-motor dual-task (CMDT) studies usually compare a single-task condition, such as a postural or walking task, with a dual-task condition, which combines the same motor task with a synchronous cognitive task. By comparing performance in both conditions, we can then calculate dual-task costs (DTCs: single-task minus dual-task performance divided by single-task performance) which indicate the degree of performance decline in one or both tasks due to limited cognitive capacity (Li and Lindenberger, 2002; Marusic et al., 2015; Janouch et al., 2018; Wollesen et al., 2018). CMDT studies have shown that as cognitive load increases during the manipulation of sensory information, older adults show greater postural performance decrements compared to their younger counterparts (Redfern et al., 2001; Doumas et al., 2008). Competition for cognitive capacity is also observed when auditory challenges are experimentally imposed on different motor tasks, such as balancing or walking (Nieborowska et al., 2019), or when older adults with hearing impairment undergo CMDT (Lau et al., 2016). The so-called “posture-first” hypothesis or strategy (Shumway-Cook et al., 1997) describes the prioritization of physical safety by allocating more attention to motor performance than to cognitive performance. In older adults, such prioritization increases with task complexity, postural threat, or fear of falling (Li et al., 2001).

Since older adults often exhibit hearing impairments that severely affect their lives, investigating the interaction between age-related hearing impairment and decline in other domains (e.g., vision, cognition, and mobility) at the behavioral and neurophysiological levels could elucidate the underlying mechanisms. In addition, this research could lead to therapeutically promising insights by providing a better understanding of the risk of falls leading toward improved fall prevention programs.

Daily dual-task situations entail different levels of cognitive complexity and therefore will require different cognitive abilities. According to Colcombe and Kramer (2003), cognitive complexity can be classified as (1) simple stimulus-response reaction reflecting processing speed (e.g., reacting to stop at a red traffic light); (2) visuo-spatial tasks to orient in the environment (e.g., walking on uneven ground or avoiding puddles, detecting and deciding whether to evade an approaching object or person), and (3) executive tasks which represent action planning, and response-inhibition (e.g., crossing a street without traffic lights while constantly adapting movement to current traffic flow or remembering a shopping list). For all these daily activities visual information processing is ubiquitous and is relevant to walking itself (Rosano et al., 2012; Mahoney and Verghese, 2018; Owsley et al., 2018). Therefore, a visual dual-task condition while walking will be used as one experimental manipulation of this study. Furthermore, growing evidence indicates that hearing has an important influence on walking performance as well (Chang et al., 2009; Viljanen et al., 2009a; Gopinath et al., 2016; Wollesen et al., 2018). Moreover, daily situations requiring executive decision-making are often solved by a multi-sensory integration including hearing (e.g., the sound of approaching cars) and not only by vision (Wollesen et al., 2021). Therefore, this study will also look at neuronal correlates of dual-task walking with an auditory secondary task. As we assume that participants with hearing impairments compared to participants with normal hearing might have more difficulties during auditory dual-task walking situations, the study will allow for more insights about possible differences in cognitive processing (i) in the different dual-task situations and (ii) between the participants with and without hearing impairments.

Previous research on cognitive-motor interference (CMI) while dual-task walking showed that spatio-temporal gait parameters like walking speed, step length, and arm swing symmetry are affected by the secondary task (Mirelman et al., 2015; Killeen et al., 2017). Moreover, there is evidence that different pre-conditions of the individuals’ cognitive-motor abilities, such as balance decline, concern about falling, and hearing impairments, negatively influence dual-task walking, that is reduced walking speed, step length, heel-strike, and foot-rolling movements (Wollesen et al., 2017a,b). These effects were maintained after controlling for age and comorbidities and showed that older adults with concerns about falling or hearing impairment have worse initial conditions on their gait quality and therefore have an increased risk of falling. More research is warranted to confirm these findings, as they relied purely on behavioral data with biomechanical walking measurements and cognitive performance through error counting or reaction times. Therefore, it is relevant to investigate the interaction between the motor and the cognitive system by analyzing the processes and conditions that influence older adults’ gait performance in situations that require concurrent performance of sensorimotor and cognitive tasks.

The following experiment will use walking tasks with different complexities and priorities, and record behavioral (spatio-temporal gait parameters) as well as neurophysiological data.

### Mobile Brain/Body Imaging to Evaluate Cognitive-Motor Interference

Mobile brain/body imaging (MoBI; Makeig et al., 2009; Gramann et al., 2011, 2014) combines mobile brain imaging (in most cases Electroencephalography; EEG) of freely moving participants with synchronized recordings of task performance and body movements. MoBI is the only brain imaging method that allows for investigating the neuronal correlates of dual-task costs during over ground walking. Motion capture provides the necessary biomechanical data as well as measures of gait quality including arm swing and hip rotation. Walking is associated with movement of the head and the eyes producing electrical activity that will, due to volume conduction, be recorded as a mixture with other active sources in the brain at the sensor level (Jung et al., 2000). Recording and analyzing EEG data from actively walking participants thus requires analysis approaches that differentiate between the brain and non-brain activity. It was demonstrated that brain dynamics can be recorded and successfully analyzed using independent component analysis (ICA) even when subjects walk or run on a treadmill (Gramann et al., 2010; Gwin et al., 2010, 2011; Seeber et al., 2013; Wagner et al., 2013, 2014). Importantly, event-related spectral perturbations (ERSPs) demonstrated a desynchronization of theta oscillation when transitioning from standing to walking while the P300 event-related potential (ERP) component revealed amplitude reductions while walking (Wagner et al., 2016). A similar reduction of an ERP component amplitude was found for the N2 in a Go/NoGo task for dual-task walking as compared to sitting with older adults revealing less pronounced component amplitudes and increased latencies compared to young adults reflecting increased dual-task costs during walking (Malcolm et al., 2015). These behavioral and brain dynamic results indicate that walking poses higher attentional demands compared to standing and thus leaves fewer resources during walking for solving a secondary task. This effect is even more detrimental for older adults with an increased difficulty to allocate attention selectively across several domains (Protzak and Gramann, 2021). Age-related sensory and cognitive decline leads to an increase in demand on attention allocation and working-memory. This was for example shown in a speech in noise perception task by Wong et al. (2009) using fMRI investigating healthy older adults.

### Previous Neurophysiological Studies in Hearing Impaired

Evidence indicates several anatomical and functional brain alterations in hearing-impaired older adults. These changes occur not only in regions involved in auditory processing but also in regions involved in attention and emotional processing (cf. Mudar and Husain, 2016). For the present study, we will further describe the brain activity alterations in individuals with hearing impairment.

Two studies by Campbell and Sharma examined auditory (Campbell and Sharma, 2013) and visual evoked potentials (Campbell and Sharma, 2014) in adults with bilateral mild to moderate high-frequency (2–8 kHz) hearing loss and normal-hearing controls. In the auditory evoked potentials study (2013), performance on a speech-in-noise test was positively correlated with increased latencies of the frontal P2 component. Compared to the control group, the hearing-impaired participants showed increases in P2 latency and amplitude. Increased activation in the frontal cortex and decreased activation in the temporal cortex in hearing-impaired subjects compared to the control group were found using cortical source localization, indicating possible changes in the allocation of cortical resources. In the study published in 2014, Campbell and Sharma examined visual evoked potentials and correlated auditory performance in a speech perception task with the visual evoked N1 latency for persons with mild-moderate hearing loss. Adults with hearing loss showed decreased N1 latencies compared to controls and a negative correlation with auditory performance. Furthermore, the amplitudes of P1, N1, and P2 were significantly larger for hearing-impaired participants (Campbell and Sharma, 2014). Using source localization, the authors showed that the P1 component originated from similar brain areas (cerebellar and higher-order visual cortical regions) for both, hearing-impaired and healthy participants. However, for the N1 and P2 components, the hearing-impaired group showed increased activation in temporal areas, which are associated with auditory processing (e.g., superior temporal gyrus, medial temporal gyrus, and inferior temporal gyrus; Campbell and Sharma, 2014). This suggests visual cross-modal reorganization (i.e., intact visual systems can recruit and repurpose deprived audio cortices for processing of their input). Similarly, Cardon and Sharma (2018) investigated cross-modal reorganization between the auditory and somatosensory modalities in older adults with normal hearing and mild-moderate hearing in response to vibrotactile stimulation using high-density electroencephalography. Results showed activation of the somatosensory areas in both hearing-impaired and adults with normal hearing. However, adults with age-related hearing impairment also showed activation of auditory cortical regions in response to somatosensory stimulation.

Regarding the current literature, existing studies with hearing impaired older adults only addressed one of the described aspects but not the comparison of the two most relevant domains for daily activities (vision and hearing) for this target group. Moreover, the neural correlates of existing studies with hearing impaired participants were only examined in a sitting condition. It remains unclear if these findings can be transferred to daily situations that reflect dual-tasking aspects during real life activities. Therefore, the multicomponent MoBI-approach will help to overcome the research gap and gain deeper insights into the neural underpinnings of the interaction of motor and cognitive tasks in different dual-task conditions (visual and auditory). We will further systematically control for the impact of age and potential performance decrements of older adults with hearing impairments.

### Aims and Research Questions for the Study

The present study is designed to investigate the following three foci using a MoBI approach:

Focus 1: General characteristics of dual-task walking of all participants.

•How does cognitive task performance differ when using visual or auditory stimuli in single- and dual-task conditions?•How are dual-task costs represented in gait parameters?•How are neuronal correlates of auditory and visual information processing impacted by dual-task interference during walking?

Focus 2: Age-related differences in dual-task walking.

•Can we replicate the age-related increase in dual-task costs?•How are the age-related differences in performance reflected in the respective brain activity of younger and older adults?•How do younger and older adults differ in their gait parameters and gait-phase related stimuli processing?

Focus 3: Differences of hearing-impaired and healthy older participants in dual-task walking.

•How do auditory vs. visual information processing and movement control vary with regards to the effect of hearing impairment represented in both cognitive task stimuli modalities and dual-task vs. single-task performance?•How are dual-task costs reflected in biomechanical and neuropsychological measures of hearing-impaired participants?

The overall hypothesis is that there are differences in dual-task costs and their corresponding neuronal correlates between the three groups with the highest disadvantages for the group of older adults with impaired hearing. We hypothesize that the performance differences are linked to the different cognitive-motor processes; i.e., information or stimulus input, resource allocation, and movement execution. Further, we hypothesize that the increasing task complexity (from single-task to dual-task), as well as the stimulus modality (visual vs. auditory), will further diminish the walking performance and increase neuronal activity.

## Methods/Study Design

This protocol paper was drafted according to the SPIRIT statement (Chan et al., 2013).

### Trial Design

This protocol will reflect a multifactorial mixed-measure design with the two two-level between-subject factors, *age* (younger vs. older adults) and *hearing impairment* (mild hearing-impaired vs. not hearing impaired). The design will be incomplete as the sample contains older adults with hearing impairments and healthy controls matched by age and gender as well as a younger age group. No data of young hearing-impaired adults will be recorded.

The within-subject factors will be the *task condition* (single- vs. dual-task) and *cognitive task modality* (visual vs. auditory). Stimuli of the cognitive task will vary according to the *presentation side* (left vs. right), *modality-specific properties* (magenta vs. cyan or low vs. high pitch, respectively), and *presentation-response compatibility* (ipsilateral vs. contra-lateral). Analyses of dual-task costs and underlying neuronal correlates can focus either on gait parameters or cognitive task performance.

The chosen colors and tone pitch levels are the conclusion of extensive piloting. In case further testing reveals that other properties are more appropriate for the experimental paradigm, we keep the option open to change the modality-specific properties.

### Participants, Interventions, and Outcomes

#### Ethical Approval

The study will be conducted in agreement with the principles of the Declaration of Helsinki and the guidelines of Good Clinical Practice. Written informed consent will be obtained from all participants before enrolment in the study. The local ethics committee of the TU Berlin, Germany, has approved the study protocol {BPN_WOL_1_210129}. The trial was registered at DRKS.de with registration number DRKS00024453 on April 14th, 2021.

#### Recruitment of Participants

To assure eligibility and recruitment of participants, community-dwelling older adults will be recruited from a database of the TU Berlin (e.g., “TUB-Versuchspersonenportal”) as well as public advertisement and collaborating audiologists in the surrounding areas of Berlin and Hamburg.

Based on sample size calculation (for details see section “Sample Size Estimate/Power Calculations”), a group of 96 community-dwelling older adults (50–70 years) and 48 younger adults (20–30 years) will be recruited. The older experimental group will be divided into the following 2 equally sized subgroups: (1) hearing impaired, (2) not hearing impaired. The participants’ allocation to the group will be done after prior assessment using a test battery in a first session. Data analyses will be done on anonymized data.

#### Confidentiality

All recorded data will be pseudonymized using a participants’ number. Only the individual participant code recreated by the participant will allow identifying the participants number of the respective data set in case data deletion is requested within thirty days after end of the data recording. No questionnaire or digital data file will include names or other personal information that would allow identification of data-participant-relations. Video recordings will be stored only after pixelating the face (e.g., Sensarea). Raw data of video will be already deleted permanently on the day of the recording as soon as the pixelating is done.

#### Eligibility Criteria

The group assignment will be based on the severity of hearing impairment using 4-frequency (0.5, 1, 2, and 4 kHz) pure-tone average (PTA 0.5–4 kHz) and defining PTA 0.5–4 kHz ≤ 25 dB HL as normal and PTA 2–4 kHz = 26–40 dB HL as mild in the better hearing ear. Participants will be asked to do the hearing acuity testing with and without their hearing aid to record if their hearing ability was corrected to normal which has effects on the sensory stimulation of the brain.

Inclusion criteria for the healthy young participants will be (1) no diagnosis of hearing impairment (PTA 0.5–4 kHz ≤ 25 dB HL), (2) age range between 20 and 30 years, (3) no color blindness.

Inclusion criteria for the non-hearing-impaired older participants will be: (1) no diagnosis of hearing impairment (PTA 0.5–4 kHz ≤ 25 dB HL), (2) score > 7 for the Short Physical Performance Battery (SPPB), (3) living independently in the community, (4) maximally moderate risk of falls (< = 13% in the QuickScreen Clinical Falls Assessment Tool), (5) age range between 50 and 70 years, (6) no color blindness.

Inclusion criteria for the hearing-impaired older participants will be: (1) diagnosis of mild hearing impairment (PTA 2–4 kHz = 26–41 dB HL), (2) score > 7 for the SPPB, (3) living independently in the community, (4) maximally moderate risk of falls (≤ 13% in the QuickScreen Clinical Falls Assessment Tool), (5) age range between 50 and 70 years, (6) no color blindness. The severity of hearing impairment will be based on the pure tone audiometry results (evaluated by qualified audiologists prior to the pre-screening session).

Exclusion criteria will be (1) severe hearing impairment (PTA 0.5–4 kHz ≥ 41 dB), (2) any acute or chronic diseases, especially of the peripheral and central nervous system, (3) recurrent falls, (4) impaired vision that is not corrected with e.g., glasses, (5) SPPB score ≤ 7, (6) indication for impaired cognition (MoCA), (7) risk of falls > 13% (QuickScreen Clinical Falls Assessment Tool).

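### Normal hearing is defined on 0.5–4 kHz but mild impairment on 2–4 kHz, so the two older groups are not mutually exclusive

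*Protocol article*

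**What the plan says.** All the cut-points stand in the protocol article, under Eligibility Criteria.

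- **Metric for assignment:** groups are formed "using 4-frequency (0.5, 1, 2, and 4 kHz) pure-tone average (PTA 0.5–4 kHz").
- **Normal and mild:** the same sentence continues "defining PTA 0.5–4 kHz ≤ 25 dB HL as normal and PTA 2–4 kHz = 26–40 dB HL as mild", judged on the better ear.
- **Non-impaired older group:** "Inclusion criteria for the non-hearing-impaired older participants will be: (1) no diagnosis of hearing impairment (PTA 0.5–4 kHz ≤ 25 dB HL").
- **Impaired older group:** "diagnosis of mild hearing impairment (PTA 2–4 kHz = 26–41 dB HL").
- **Exclusion:** "severe hearing impairment (PTA 0.5–4 kHz ≥ 41 dB").
- **Basis for severity:** "The severity of hearing impairment will be based on the pure tone audiometry results".

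Under Recruitment of Participants, "The older experimental group will be divided into the following 2 equally sized subgroups: (1) hearing impaired, (2) not hearing impaired". The Statistical Analysis section uses hearing ability as a between-subject factor among older adults, and Focus 3 of the aims is the comparison of these two groups.

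**The concern.** Normal hearing and the exclusion rest on the average of four frequencies. Mild impairment rests on the upper two only, and this is stated twice. A loss confined to the higher frequencies raises the two-frequency average about twice as fast as the four-frequency average, so the two rules can disagree about the same ear. No sentence says which prevails.

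Hearing status is the only thing that separates the two older groups. If one audiogram satisfies both definitions, membership for that person depends on something the protocol does not state. If such people go into the impaired group, it contains participants who meet the protocol's own standard of normal hearing. If they go into the control group, it contains participants who meet its standard of mild loss. Either way the contrast can shrink. If placement differs from person to person, it can also be biased.

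The band matters for interpretation too. The auditory task uses tones of 500 and 1000 Hz (Cognitive Tasks While Sitting), which are the frequencies that the 2–4 kHz definition leaves out.

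**Working it through.** **Inputs** (Eligibility Criteria, better ear): normal if the 0.5–4 kHz average is ≤ 25; mild if the 2–4 kHz average is 26–40 (41 in the inclusion criterion); excluded if the 0.5–4 kHz average is ≥ 41. The example audiograms are assumptions that show such cases exist. The protocol reports no audiogram data, and it has no figure of its own to reproduce here.

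**Notation.** L = mean of the 0.5 and 1 kHz thresholds; H = mean of the 2 and 4 kHz thresholds. The four-frequency average is (L + H)/2.

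- Normal: (L + H)/2 ≤ 25, that is L + H ≤ 50.
- Mild: 26 ≤ H ≤ 40.
- Excluded: (L + H)/2 ≥ 41, that is L + H ≥ 82.

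**Overlap of normal and mild.** Both hold when 26 ≤ H ≤ 40 and L ≤ 50 − H.

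| L (dB HL) | Range of H meeting both definitions |
|---|---|
| 10 or less | 26–40 (every mild candidate) |
| 15 | 26–35 |
| 20 | 26–30 |
| 24 | 26 only |
| above 24 | none |

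Everyone in the overlap therefore has a mean threshold of at most 24 dB HL at 0.5 and 1 kHz, the frequencies of the auditory stimuli.

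**Examples** (thresholds at 0.5/1/2/4 kHz):

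| Audiogram | 0.5–4 kHz average | 2–4 kHz average | Status under the text |
|---|---|---|---|
| 10/15/30/40 | 95/4 = 23.75 | 70/2 = 35 | normal and mild |
| 20/25/25/30 | 100/4 = 25 | 55/2 = 27.5 | normal and mild |
| 45/45/40/40 | 170/4 = 42.5 | 80/2 = 40 | mild and excluded |
| 20/20/45/55 | 140/4 = 35 | 100/2 = 50 | neither group, not excluded |

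**How much of the space overlaps.** Take every audiogram on a 5 dB grid from 0 to 80 dB whose thresholds do not improve with frequency. Of these, 410 patterns meet both definitions, 293 normal only and 219 mild only. So 410 of the 410 + 219 = 629 patterns meeting the mild rule also meet the normal rule. The grid weights all patterns equally. It shows that the overlap is not a corner case of the rules, but it is not a prevalence.

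**Mild and excluded together.** With H at most 40, exclusion needs L of at least 82 − 40 = 42, so hearing must be worse at the low frequencies. No pattern on the non-improving grid does this.

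**The 40/41 limits.** If thresholds are taken in 5 dB steps (an assumption; the protocol gives no step size), the 2–4 kHz average moves in steps of 2.5 dB (40, 42.5) and the four-frequency average in steps of 1.25 dB (40, 41.25). Neither can equal 41, and the grid counts are identical with either limit.

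**The case against.** **2–4 kHz may be a slip for 0.5–4 kHz.** That is possible, and the announced metric supports it. But the narrower band appears twice and is nowhere corrected. It could also be deliberate, since the background reviews studies of high-frequency (2–8 kHz) loss. A reader cannot tell which is meant, and a slip would still need correcting.

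**The diagnosis settles it.** Controls must have no diagnosis of impairment, and audiologists evaluate severity before the pre-screening session. On one reading, a person found mildly impaired on 2–4 kHz cannot be a control. But each diagnosis is specified by its own average in parentheses, so someone at 23.75 on four frequencies equally has no diagnosis by the control criterion. What stands is that the text is ambiguous. It does not show that staff would assign people arbitrarily.

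**People in neither group.** A reader might count audiograms such as 20/20/45/55 as a further source of bias. The documents do not support that. Inclusion criteria need not cover everyone; such a person is not enrolled and does not affect the contrast.

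**The value 41.** A reader might infer that people at exactly 41 dB are both admitted and excluded. That needs both averages to be 41, which cannot occur with 5 dB steps. The discrepancy is real but editorial.

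**Size.** The algebra shows that overlap is possible, not how often it occurs at ages 50–70. That objection stands in full.

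**Conclusion.** The point holds for the band mismatch. As written, the two levels of the hearing factor in Focus 3 and in the ANOVA are not mutually exclusive: anyone with H of 26–40 and L + H ≤ 50 qualifies for both older groups, and no rule decides between them. This follows from the stated cut-points alone. It is a contradiction in the text, not a detail left to a fuller document.

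The effect on the contrast may be dilution or bias. Its size depends on how many recruits have sloping losses and where they are placed, and the documents give neither. A claim that a given share of participants will be misclassified would go beyond them.

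Two lesser inconsistencies belong with it. A person can meet the mild criterion and the exclusion at once, although only with a loss that is worse at low frequencies. The upper limit of mild is 40 in the definition and 41 in the inclusion criterion, while exclusion begins at 41.

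**What to change.** Reconcile the statements so that normal, mild and excluded use one frequency band and one set of non-overlapping limits, in the assignment sentence, the inclusion criteria and the exclusion alike. Two routes would do it:

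1. **One band.** The four-frequency average is the natural candidate, because the protocol itself announces it for group assignment. No audiogram could then fall in both groups. With 5 dB steps, no average would fall strictly between 25 and 26 or between 40 and 41.
2. **Keep 2–4 kHz for mild, if that is intended.** The normal group must then also be required to lie below the mild limit on 2–4 kHz, and the exclusion must be stated so that it cannot overlap mild.

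On either route, give a single upper limit for mild in place of 40 and 41.

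**Cost.** No new measurement is needed, because the same audiogram supplies every value. But this is more than wording, since the choice of band changes somewhat who counts as impaired. On the four-frequency average, some high-frequency-only losses (10/15/30/40, at 23.75) would count as normal, and some steep losses now in neither group (20/20/45/55, at 35) would count as mild. The investigators should decide which population Focus 3 is about. If anyone has already been classified, they should re-derive that person's group under the reconciled rule.
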